## Methods

### Study design

The study is designed as a randomized controlled, single-center, and single-blinded trial, in which participants will be randomly assigned to one of two intervention groups (rumination vs. self-compassion) or a control condition (see “Randomization”) with an allocation ratio of 1:1:1. The study employs a superiority trial design, aiming to determine whether one of the two cognitive coping interventions is more effective in modifying the responsiveness and habituation of biological stress systems compared to the control condition. The design encompasses repeated measurements of each group, i.e., each group will undergo two experimental sessions (t1 and t2) comprising stress test exposures, and within each experimental session, repeated biological and psychological outcome assessments will take place (see Table 1).

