### Hypotheses

By increasing either ruminative or self-compassionate thoughts among healthy young adults, the intervention programs are expected to affect the regulation of occurring emotions as expressed by the responsiveness of biological systems during repeated stress exposure.

To check whether the experimental manipulations are successful on a psychological level, self-report measures will be assessed repeatedly over the course of each experimental session and are expected to change over the course of experimental sessions 1 and 2. Specifically, we hypothesize that stress will elicit changes in affect scores and stress appraisals, whereas the two intervention programs are expected to induce changes in affect, self-compassion and rumination, which will be stronger than in the control group (no intervention). Furthermore, we expect these variables to predict indicators of biological stress system activity.

Hypothesis 1: Independent of experimental session and group, stress will elicit significant increases of negative affect and stress appraisals as well as decreases of positive affect.Hypothesis 2: At experimental session 1, stress-induced changes of positive and negative affect and stress appraisals will be indifferent between participants from intervention groups 1 (rumination) and 2 (self-compassion) as well as participants from the control group (no intervention).Hypothesis 3: At experimental session 2, stress-induced decreases of positive affect as well as increases of negative affect and stress appraisals will be strongest in participants from intervention group 1 (rumination) and lowest in participants from intervention group 2 (self-compassion).Hypothesis 4: Increases in state self-compassion and positive affect from pre- to post-intervention will be strongest in intervention group 2 (self-compassion), and increases in state rumination and negative affect will be strongest in intervention group 1 (rumination).

Furthermore, we expect significant responses of biological stress system activity in all experimental groups at each experimental session. Specifically, we expect responses of biological stress system activity to be similar at experimental session 1 and participants from intervention group 2 (self-compassion) to show stronger habituation of stress system activity compared to intervention group 1 (rumination) or the control group (no intervention).

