Hypothesis 5: Independent of experimental session and group, stress elicits significant responses of biological stress system activity.Hypothesis 6: At experimental session 1, responses of biological stress system activity will be indifferent between participants from intervention groups 1 (rumination) and 2 (self-compassion) as well as participants from the control group (no intervention).Hypothesis 7: At experimental session 2, responses of biological stress system activity will be strongest in participants from intervention group 1 (rumination) and lowest in participants from intervention group 2 (self-compassion).Hypothesis 8: Habituation of biological stress system activity will be lowest in participants from intervention group 1 (rumination) and strongest in participants from intervention group 2 (self-compassion).Hypothesis 9: Self-compassion and positive affect will predict lower biological responses to repeated stress, whereas rumination, negative affect, and stress appraisals will predict higher biological responses to repeated stress.Hypothesis 10: Self-compassion and positive affect will predict stronger habituation of biological stress system activity to repeated stress, whereas rumination, negative affect, and stress appraisals will predict lower habituation of biological stress system activity to repeated stress.

We expect these changes to occur among markers of the HPA axis, the autonomic system, as well as the inflammatory system.

Associations of biological stress system activity with other psychological variables (e.g., emotion regulation, coping) as well as demographic (e.g., age, gender, sex) and anthropometric (e.g., BMI) variables will be tested in an exploratory fashion.

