### Data preparation and statistical analysis

Data preparation and statistical analysis will be performed using IBM SPSS Statistics 26 (IBM Corp., Armonk, NY, USA). Following our pre-registered analysis plan [60], data will be screened for outliers using *z*-scores, and outliers which differ more than 3 standard deviations from the participants’ mean will be excluded from further analysis. In addition, participants will be excluded in case of elevated cortisol levels (e.g., > 12 nmol/L or *z* > 3.29) after arrival at the laboratory (i.e., at baseline) and after accommodating to the testing situation (i.e., at − 1 min relative to the TSST). Additionally, non-adherent participants whose missing values exceed 25% of the data will also be excluded from the analysis. In the next step, Kolmogorov–Smirnov tests will be conducted in order to check for normal distribution. If necessary, data will be log-, ln-, or inverse transformed to reduce skewness of biological data.

To analyze the data (i.e., to compare self-report measures as well as biological response and habituation indices between experimental groups), we will use separate analyses of covariance (ANCOVAs). Sex and BMI will be used as covariates in analyses of biological data, as these two variables have been repeatedly shown to be highly relevant for stress system activity [61, 62]. We will use the standard *p* < 0.05 criteria for determining if the ANCOVA and the post hoc test suggest that the results are significantly different from those expected if the null hypothesis were correct. The post-hoc Bonferroni test adjusts for multiple comparisons.

To investigate associations between primary psychological outcome measures and indices of biological stress measures, we will compute separate hierarchical linear regression models, regressing biological outcome measures onto psychological outcome variables. Again, sex and BMI will be included as covariates in these analyses. When examining state variables, the respective trait variable will be included as covariate in regression analyses.

We expect that certain psychological (e.g., emotion regulation, coping), demographic (e.g., age, gender, sex), and anthropometric (e.g., BMI) variables may be related to biological stress system activity. Therefore, we will test for relationships between these variables and primary outcome measures of biological stress responses in an exploratory fashion.

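### Hypotheses 2 and 6 predict no difference between arms at session 1, but the only criterion shown is a difference test at p < 0.05, which can reject them and cannot support them

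*Protocol article*

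**What the plan says.** All references are to the protocol article.

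- **Hypotheses.** Two of the ten numbered hypotheses predict no difference between the three arms at session 1. Hypothesis 2: "stress-induced changes of positive and negative affect and stress appraisals will be indifferent between participants" of the two intervention groups and the control group. Hypothesis 6: at session 1, "responses of biological stress system activity will be indifferent between participants from intervention groups 1 (rumination) and 2 (self-compassion") and the control group. Neither has a margin or is labelled a descriptive check.
- **Study design.** "The study employs a superiority trial design".
- **Primary outcomes.** Response indices are computed for both the initial and the repeated stress exposure, so session-1 indices are among the analysed outcomes. The habituation index is the first response minus the second.
- **Data preparation and statistical analysis.** For comparing self-report measures and biological indices between groups, "we will use separate analyses of covariance (ANCOVAs"), with sex and BMI as the covariates for biological data. On the decision rule: "We will use the standard *p* < 0.05 criteria" to judge whether results differ significantly from the null expectation. On post hoc tests: "The post-hoc Bonferroni test adjusts for multiple comparisons".
- **Power analysis.** The sample size of 111 (37 per arm, raised to 120) rests on expected differences in habituation.

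**The concern.** A difference test starts from equality and looks for evidence against it. A p-value of 0.05 or more means only that such evidence was not found, and in a small sample that is compatible with differences of moderate size. As written, Hypotheses 2 and 6 therefore have a stated way to fail and no stated way to succeed.

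At stake is what the trial may say about two of its ten hypotheses. The text introducing Hypotheses 5 to 8 places similar session-1 responses next to the habituation prediction, and the session-1 response is itself one term of the habituation index. A report of no significant session-1 difference could give more reassurance about that term than the data contain.

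**Working it through.** **Inputs.** 37 per arm, N = 111, three groups, alpha 0.05, power 0.80, planning effects d = 0.67 and 0.81 (Power analysis); two covariates and Bonferroni post hoc tests (Data preparation and statistical analysis). Differences are in SD units. Equivalence margins are assumed.

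**1. The plan's sample size.** For a three-group F test, the noncentrality is f² × N. With f = 0.30 this is 0.09 × 111 = 9.99, and power is 0.8035 without covariates and 0.8033 with two. N = 111 is thus reproduced. The article prints the effect as f² = 0.30; taken literally, that would give N = 36. The calculation is used here only to fix 37 per arm.

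**2. Precision of a session-1 comparison.** SE = √(2/37) = 0.232 SD. The 95% half-width, using t on 72 degrees of freedom, is 0.46 SD; the 90% half-width is 0.39 SD.

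**3. What a non-significant result leaves open.** If one arm truly differed from the other two by 0.5 SD, f = 0.236. The omnibus test with two covariates would then be non-significant 42% of the time. For a single pair, power at d = 0.5 is 0.564 unadjusted and 0.387 at 0.05/3, so the difference is missed 44% and 61% of the time.

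**4. What an equivalence test could show.** Two one-sided 5% tests, true difference zero. In the normal approximation, 80% power needs a margin of (1.645 + 1.282) × 0.232 = 0.68 SD. Simulation with estimated variance gives 0.69 SD (0.66 SD at 40 per arm).

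| Assumed margin (SD) | Power per pair, 37 per arm | All three pairs, 37 per arm | n per arm for 80% per pair |
|---|---|---|---|
| 0.3 | 0% | – | 191 |
| 0.4 | 7% | – | 108 |
| 0.5 | 37% | 13% | 69 |
| 0.6 | 64% | – | 48 |
| 0.67 | 77% | 56% | 39 |
| 0.81 | 93% | 84% | 27 |

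(– = not computed.)

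**5. How the rule behaves when Hypothesis 6 is true.** Each test still rejects 5% of the time. Across the nine biological markers, the chance of at least one rejection is 1 − 0.95⁹ = 0.37 if they were independent. Related markers would change that figure.

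**6. Which session-1 measures randomisation covers.** The Abstract places assignment immediately after the first stress induction. The Randomization section has allocation drawn before testing. Experimental setting and procedure describes assignment after listing the samples. Session-1 blood is drawn at +30 min and again at +90 min (Table 2) or +120 min (Experimental setting and procedure). Affect is also rated at +20 and +120 min. The text shown does not fix when the writing task falls relative to these points. Five of the nine markers (plasma IL-6 and four expression rates) come from the blood samples.

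**The case against.** **A reader might infer that the investigators will treat p ≥ 0.05 as proof of equality.** The documents do not say so. They use p < 0.05 only to call results different. They also refer to a pre-registered analysis plan, not shown, that may hold further criteria. What stands is narrower: no criterion shown could support Hypotheses 2 and 6.

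**A reader might infer that 37 per arm cannot show similarity at all.** That depends on the margin. At 0.81 SD, power is 93% per pair and 84% for all three pairs. Non-appearance on day 2 does not remove session-1 data, so up to 40 per arm may be available. However, 0.81 SD is the larger effect the trial is planned around, so equivalence within it would say little about useful similarity.

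**A reader might infer that any session-1 difference is chance by design, so the miss rates in step 3 concern differences that cannot exist.** For measures taken before the writing task, randomisation does make the arms equal in expectation, and step 3 then shows only how little a non-significant result conveys. For the late blood samples and affect ratings the inference is not secured, because the task's timing is not fixed. The analysis section also excludes participants after randomisation (outliers, high cortisol, more than 25% missing), so the analysed arms need not be exactly the randomised ones.

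**The strongest objection is that little depends on this.** No later analysis is conditional on Hypotheses 2 or 6, the sample size does not rest on them, and randomisation protects the session-2 and habituation contrasts from systematic bias. This stands, and it limits the weight of the point.

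**Conclusion.** The point holds in limited form. Hypotheses 2 and 6 predict no difference, while the only rule shown can reject them and not support them. At 37 per arm, a pairwise session-1 difference is known to within about ±0.46 SD, and equivalence has 80% power per pair only from a margin of about 0.69 SD, close to the smaller planning effect of 0.67. The precision figure rests on 37 analysed per arm. The equivalence figures also assume a true difference of zero and margins that the documents do not give.

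The effect on Hypotheses 7 and 8 is small and the point is minor. It concerns what may be concluded on two of the ten hypotheses, not the validity of the main contrasts.

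**What to change.** 1. Recast Hypotheses 2 and 6 as expected comparability at session 1, and state that p ≥ 0.05 does not confirm them. Report session-1 changes and responses by arm, with confidence intervals for the arm differences.
2. If a similarity claim is kept, replace the p < 0.05 rule for it with two one-sided tests against a stated, justified margin. Add that margins below about 0.7 SD have under 80% power per pair at 37 per arm.
3. Limit any statement that the arms are comparable by randomisation to measures taken before the writing task. State when the task takes place relative to the late blood samples and affect ratings, and reconcile the +90 and +120 min entries.
4. Do not say that residual session-1 imbalance is handled in the session-2 model unless the session-1 response is added as a covariate. The biological analyses currently name only sex and BMI.

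Items 1 and 3 cost a few sentences and no data collection. Item 2 adds a margin and its justification. Adding the covariate in item 4 would change the model and is optional for this point. The protocol plans no analysis before data collection ends, so all of this can still be prespecified.

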### Sample handling and laboratory analysis of biological samples

Saliva samples will be stored for later analyses at –30°C after each experimental session. Upon completion of the entire data collection, the frozen salivettes will be thawed and centrifuged at 2000*g* and 20°C for 10 min. Salivary cortisol concentrations will be determined—as described by Janson and Rohleder [55]—in duplicate using a commercially available chemiluminescence immunoassay (IBL, Hamburg, Germany). Final measurements of sAA concentrations will be completed—as described by Kuras et al. [56] and Rohleder and Nater [57]—using an enzyme-kinetic method. Analogous to our previous studies [e.g., 58], peripheral immune responses to stress will be assessed via blood samples which will be centrifuged immediately at 2000*g* and 4°C. Plasma will then be aliquoted and stored for later analyses at − 80°C. IL-6 concentrations will be determined using a commercial high-sensitivity enzyme-linked immunosorbent assay (R&D Systems, Wiesbaden-Nordenstadt, Germany).

As was successfully implemented in our previous studies [e.g., 59], cytokine expression of pro- and anti-inflammatory proteins will be used to map intracellular regulation of inflammation. For this purpose, blood samples will be stored at − 80°C until RNA isolation using a commercial RNA isolation kit (Tempus Spin RNA Isolation Kit; ThermoFisher Scientific, Darmstadt, Germany). Aliquots will then be stored at − 80°C until processing. Extracted RNA concentration will be assessed with the Infinite M200pro (Tecan, Zürich, Switzerland) using NanoQuant plates™ (Tecan, Zürich, Switzerland). RNA will be translated into cDNA with the T100TH Thermal Cycler (Bio-Rad, Munich, Germany) using a commercially available High Capacity cDNA RT KIT (ThermoFisher Scientific, Darmstadt, Germany). cDNA will be diluted with nuclease-free, steam-sterilized water (Carl Roth, Karlsruhe, Germany) resulting in 35 ng cDNA per 8 µl template (reference range of ThermoFisher Scientific: 10–100ng). Real-time PCR will be performed with the ABI Prism 7000 Sequence Detection System (Applied Biosystems, Darmstadt, Germany). TaqMan™ Gene Expression Master Mix (ThermoFisher Scientific, Darmstadt, Germany) will be applied for 20 µl probe dilution per well. Cycler conditions will be applied following the manufacturer’s standard protocol. To detect the presence of complementary nucleic acids, commercially available FAM-labelled primer variants will be used (IL-6: Hs00174131_m1, IL-1β: Hs01555410_m1, RELA: Hs00153294_m1, NFKBIA: Hs00153283_m1; ThermoFisher Scientific, Darmstadt, Germany). VIC-labelled GAPDH (Primer-Limited, Hs99999905m1; ThermoFisher Scientific, Darmstadt, Germany) will be used as housekeeping gene and endogenous control. All expression levels will be determined in duplicates. Relative quantification will be assessed via measurement of fluorescence signals of FAM and VIC that accelerate proportionally to resulting PCR products. Data will be normalized against GAPDH gene expression using the ΔΔCT method (ΔΔCT = ΔΔCT target—ΔΔCT control) and expression will be normalized to the baseline for each experimental session. Upon completion of laboratory analyses, deidentified biological specimens will be preserved for potential re-analyses at the Laboratory of the Chair of Health Psychology.

### Analysis of heart rate variability

To determine autonomic responses, HR and HRV parameters will be recorded by using HRV sensors (Portabiles, Erlangen, Germany) which enable recordings of one-channel ECG signals with a 256-Hz sampling frequency. The ECG signal will be derived using dry electrodes being integrated into a chest strap. Both sensor and strap will be attached to the participant at the beginning of each experimental session to record time-dependent changes in HR and HRV using time- (RMSSD) and frequency-based (high frequency) parameters. Five-minute intervals (− 10 min pre-TSST, TSST 1, TSST 2, TSST 3, + 10 min post-TSST) will be chosen for data analysis. Data transfer will be carried out using the application “Portabiles Study Center” for Android mobile devices (Redmi 10, Xiaomi, Beijing, China).

### Randomization

Before testing, eligible patients will be randomized and stratified for sex using the Robust Randomization App (RRApp, Version 3.0.1). A principal investigator, who is independent of the enrollment and data collection, will be responsible for the randomization process. He will store the randomization lists in sealed envelopes and hand them out to staff members immediately before the experimental sessions begin. Participants will be blinded and will not know the experimental condition to which they have been assigned. Staff members will be encouraged to maintain blinding as far as possible. The actual allocation will not be disclosed to the participants, and any code breaks must be promptly reported, along with the reason for the breach. Unblinding of participants will result in study discontinuation. To assess the effectiveness of the blinding procedures, as well as to gain insight into participant perceptions of their assigned interventions, participants will be asked whether they have any suspicions about which intervention group they have been assigned to upon completion of all laboratory sessions. As the analyst is also involved in the data collection process and therefore possesses knowledge of the participants’ group assignments, no double-blinding will be implemented for the data analysis. This potential for bias will be mitigated by adhering strictly to the pre-registered analysis plan [60], which outlines the statistical methods and criteria for evaluating outcomes.

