**Methods:**

In this study, a total of 120 healthy adults will complete the Trier Social Stress Test (TSST) on two consecutive days. Immediately after the first stress induction, participants will be randomly assigned to two experimental conditions designed to manipulate cognitive coping strategies (rumination vs. self-compassion) or a control condition. Measures of HPA axis (salivary cortisol) and autonomic activity (salivary alpha amylase, heart rate, heart rate variability) as well as inflammatory markers (plasma interleukin(IL)-6, expression rates of pro- and anti-inflammatory cytokine genes) will be repeatedly assessed throughout the experimental sessions. Response and habituation indices of these measures will be calculated and compared between the experimental conditions and the control condition.

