All participants will then be randomly assigned to one of two intervention programs (intervention group 1: rumination, intervention group 2: self-compassion) or to a control condition. Participants will then receive verbal and written instructions for the upcoming task and will be asked to either engage in coping behavior (rumination vs. self-compassion) or to think neutrally about a given topic (e.g., description of everyday life) and to write down their thoughts. To check whether the experimental manipulations were successful, psychological variables will be measured repeatedly before and after each experimental condition via questionnaires (see “Psychological assessments during the experiment”). Upon completion, participants will be dismissed and reminded of the follow-up appointment (+ 1 day) and the incentive they will receive via email. With this email, participants will receive instructions to reflect on the experienced stress situation, to review and complete their notes, and to bring these notes to session 2.

The following day, participants will be scheduled at approximately the same time for experimental session 2. Procedures will closely follow those of experimental session 1, with participants being instructed to review their notes from the previous session and engage in a slightly modified version of the mental arithmetic task during the TSST (i.e., serially subtracting 13 from 2011). In contrast to experimental session 1, no further intervention will take place on this day. At the end of this session, participants will be debriefed and dismissed. To ensure quality control of the experimental procedure, regular audits will take place at intervals of 6 to 8 weeks. These audits will be conducted by a principal investigator who is independent of the data collection process. The audits will include re-training sessions for the TSST panel, as well as for staff members who interact with participants. The objective of these audits is to reinforce adherence to the protocol, address any procedural deviations, and maintain a high standard of data integrity throughout the study.

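### The protocol gives two conflicting times for randomisation and states nothing that keeps the allocation concealed until the session-1 stress response is recorded

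*Protocol article*

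**What the plan says.** The protocol article describes the time of allocation in three places.

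- Randomization: "Before testing, eligible patients will be randomized and stratified for sex using the Robust Randomization App". A principal investigator independent of enrolment and data collection runs the process, and then: "He will store the randomization lists in sealed envelopes and hand them out to staff members immediately before the experimental sessions begin".
- Abstract, Methods: "Immediately after the first stress induction, participants will be randomly assigned to two experimental conditions" or to a control condition.
- Experimental setting and procedure, after the account of the session-1 TSST and its sampling: "All participants will then be randomly assigned to one of two intervention programs" or to the control condition.

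On blinding, Study design states: "The study is designed as a randomized controlled, single-center, and single-blinded trial". The Randomization section adds: "Participants will be blinded and will not know the experimental condition to which they have been assigned". For staff it says only: "Staff members will be encouraged to maintain blinding as far as possible". It also discloses that the analyst takes part in data collection and knows the group assignments.

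Under Primary outcomes, the habituation index is the first stress response minus the second. Hypotheses 2 and 6 state that session-1 responses, psychological and biological respectively, do not differ between the three groups.

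**The concern.** Session 1 serves as the baseline in this trial. Its response enters every habituation index, and the claim that the groups start out alike rests on it. It is a clean baseline only if nobody who can influence it knows the arm while it is being measured. The TSST is delivered by people, through verbal instructions, a panel and correction of arithmetic errors, so their conduct is a possible route for bias.

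Assignment after the first TSST would protect the part of session 1 that comes before the intervention. Randomisation before testing, with lists passed to staff just before the sessions, protects it only if the envelopes stay closed, and the article does not say that they do. If a list covers more than one participant, opening it for one person would also show later allocations.

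**Working it through.** The plan states no figure on this point, and the sample size plays no part in it. The check is first a comparison of the text, then an illustration on assumed values.

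**Text**

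1. *When is a person randomised?* The Randomization section says before testing. The abstract and the procedure section say after the first TSST. The Participants section also uses the phrase about testing for what happens ahead of the laboratory visits, so the natural reading is before session 1. Read literally, the statements cannot all be true.
2. *What do staff hold before session 1?* Randomisation lists in sealed envelopes.
3. *When is an envelope opened, and by whom?* Not stated in the text.
4. *Is staff blinding required?* It is encouraged, not required.
5. *Who are the staff?* The passage on audits in the procedure section names the TSST panel separately from staff who interact with participants. Nothing says that the panel receives the allocation, and nothing says that it does not.

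**Illustration (assumed values, none from the documents)**

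Suppose knowledge of the arm shifts one arm's session-1 response by b response SDs and leaves session 2 unchanged. An equal shift in both sessions would cancel in the index. With equal SDs in both sessions and between-session correlation ρ:

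- SD of the index = √(2(1 − ρ)) response SDs
- shift in the habituation contrast: d = b / √(2(1 − ρ))

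The false-positive rate is that of one unadjusted two-sided 5% comparison with 40 per arm (normal approximation).

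| ρ | b = 0.1 | b = 0.2 | b = 0.3 |
|---|---|---|---|
| 0.3 | d = 0.085; 6.7% | d = 0.169; 11.8% | d = 0.254; 20.5% |
| 0.5 | d = 0.100; 7.3% | d = 0.200; 14.5% | d = 0.300; 26.9% |
| 0.7 | d = 0.129; 8.9% | d = 0.258; 21.1% | d = 0.387; 41.0% |

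The Power analysis section plans on d = 0.81 for cortisol and d = 0.67 for salivary alpha-amylase. At ρ = 0.5, shifts of 0.1 to 0.2 SD amount to between 0.1/0.81 = 12% and 0.2/0.67 = 30% of those effects.

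**Would the trial's own check reveal it?** Hypothesis 6 compares session-1 responses between arms. With 40 per arm, a pairwise 5% test detects a true difference of 0.1 SD with about 7% power and one of 0.2 SD with about 14%. A non-significant result would offer little reassurance.

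**The case against.** The strongest reply is that the accounts can be reconciled. The independent investigator could generate the sequence beforehand and hand it over sealed, and it could be revealed only when the writing task is assigned. Holding a sealed envelope is not knowing what is in it. The flow diagram and Table 1 were not visible in the text reviewed and may give the order. A condensed article may also leave the opening step to the full protocol. This reply stands in part: the reconciled reading is plausible and may well be the intended one. It does not remove the conflict, because the Randomization section says that people are randomised before testing, not merely that a sequence is generated. The point rests on two incompatible statements, not on a missing detail.

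A reader might infer three stronger things that the documents do not support.

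- *That staff or the panel know the arm during the first TSST.* The envelopes are sealed, the panel is named separately from participant-facing staff and must stay neutral without giving feedback, and audits with re-training take place every 6 to 8 weeks.
- *That foreknowledge allows selective scheduling.* Those randomised are already eligible, and the handover comes immediately before the sessions. Only an open, study-wide list released early would permit it, and the text does not describe one. The lists could be per stratum or per participant.
- *That the habituation results are biased by a known amount.* The shift and the correlation are assumptions. Bias would also need staff who know the arm to act on it in an arm-specific direction at session 1.

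**Conclusion.** The contradiction over the time of randomisation is real, and as written the article does not guarantee concealment of the allocation until the session-1 response is recorded. This is a gap in protection, not evidence of bias. Its possible size, d = 0.08 to 0.39 on the habituation contrast, depends wholly on an assumed session-1 shift of 0.1 to 0.3 SD confined to one arm and an assumed correlation of 0.3 to 0.7. If the envelopes are in fact opened only after the pre-intervention measures, the size is zero and only the wording needs correcting. The matter still deserves correction, because session 1 is half of every habituation index, the planned session-1 comparison has little power to expose small shifts, and the core remedy is cheap.

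**What to change.** Reconcile the Randomization section with the abstract and the procedure section:

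- The independent principal investigator generates the sequence in advance and supplies one opaque, numbered envelope per participant within each sex stratum, not a list.
- The envelope is opened only after the session-1 assessments that precede the intervention, and by the staff member who gives the writing instruction.
- The TSST panel is not given the allocation.
- Sample handlers are kept unaware of the arm at both sessions only where existing staffing allows.
- The report states which procedure was used for participants tested before the change. Data collection is planned to run until September 2026, so the correction can still protect later participants.

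The cost is a few sentences and the repacking of existing lists, with no extra visits or participants. Keeping sample handlers unaware may need a separation of roles that the article does not show to be available, which is why that item is conditional.

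One limit remains. The late session-1 blood sample is set at +90 min in Table 2 and at +120 min in the procedure section, and these need to be reconciled. Either may fall after the intervention has started. Delayed opening cannot protect such a sample, so the fix may not fully cover the inflammatory indices.
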